### Proposed sample size

The sample size of 240 will provide adequate power to detect a standardised mean difference of 0.40 in the primary outcome (RMDQ; 5% significance, 80% power) assuming attrition of 20%. Using data from Critchley *et al* (2007) and our own initial feasibility study,^57^
^30^ this equates to a 2-point difference between groups, where a 2–3 point difference in the RMDQ score is considered clinically important.^51^ It is hoped attrition will be minimised by a full explanation prior to recruitment of the time commitment required and importance of completing all follow-up questionnaires. A protocol will be developed to ensure an optimum and standardised follow-up process, including recording multiple contact addresses, email addresses and phone numbers.

Planned secondary analysis will be performed to determine whether the treatment effect occurs via changes in the process variables as hypothesised (pain acceptance and committed action). Specifically, the proportion of the treatment effect for disability (RMDQ), QoL (WSAS) and mood (PHQ-9 and GAD-7) at each follow-up that is mediated by the treatment effect on the process variables at 3 months will be determined. This will be estimated by the product of coefficients method using bootstrapped SEs.^57^ This analysis will be undertaken irrespective of achieving the statistical significance. Where the treatment effect is non-significant, additional further analysis will be conducted to determine the role of post-randomisation effect modifiers in the negative result (adherence, treatment fidelity and therapeutic alliance). For example, should there be considerable non-adherence to the treatment, the efficacy of the treatment for those who adhere to treatment will also be estimated in terms of the complier average causal effect (CACE).

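### The mediation result is fixed as a proportion of the treatment effect whatever the size of that effect; the ratio is mostly usable at the planned effect, but not at a small or null one

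*Protocol article*

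**What the plan says.** The planned secondary analysis in the Statistical analysis section of the protocol article asks whether the treatment works through pain acceptance and committed action. Its target is "the proportion of the treatment effect for disability (RMDQ), QoL (WSAS) and mood (PHQ-9 and GAD-7) at each follow-up that is mediated", where the mediating path runs through what treatment does to those two variables at 3 months. That makes four outcomes at two follow-ups, so eight total effects serve as denominators.

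On method, the article states: "This will be estimated by the product of coefficients method using bootstrapped SEs". On conditions: "This analysis will be undertaken irrespective of achieving the statistical significance".

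The next sentence foresees a null result: "Where the treatment effect is non-significant, additional further analysis will be conducted to determine the role of post-randomisation effect modifiers". It adds analyses for that case, including a complier average causal effect, but leaves the proportion as it stands. No condition is placed on reporting it, and the indirect effect in outcome points is not named as a result.

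**The concern.** A proportion of an effect has a clear meaning only if there is an effect and its direct and indirect parts point the same way. If the total effect is close to zero, small sampling changes in the denominator move the ratio from large positive to large negative values. Bootstrapping does not cure this, because the spread of such a ratio has no stable value to estimate.

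Understanding how improvement comes about is a listed secondary objective, and the article counts evidence on mechanisms among the study's strengths. Followed as written, the plan could answer that objective with a figure such as -200% or 400% mediated. It could also give a plausible-looking percentage of an effect that was never shown to exist.

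**Working it through.** **Inputs from the article.** The Proposed sample size section claims "adequate power to detect a standardised mean difference of 0.40 in the primary outcome" at 5% significance and 80% power with 20% attrition, and says "this equates to a 2-point difference between groups". The implied SD is 2 / 0.40 = 5 points. With 120 per arm and 20% attrition, 120 x 0.8 = 96 per arm remain.

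**The plan's own figure.** With a two-sided 5% test (assumed), n per arm = 2 x (1.96 + 0.84)^2 / 0.40^2 = 98, or 99 with unrounded quantiles and rounding up, so 198 in total. Multiplying by 1.2 gives 238; dividing by 0.8 gives 248. Power at 96 per arm is 0.79. The stated 240 is therefore reproduced closely enough. It also follows that about one trial in five is non-significant even if the true effect is 2 points.

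**Size of the denominator's error.** SE of the total effect = 5 x sqrt(2/96) = 0.72 points. An observed effect smaller than 1.96 x 0.72 = 1.41 points is non-significant, and the proportion would still be computed.

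**Simple illustration.** Take an indirect effect of -0.5 points and a true total of -1 point (50% mediated). If the observed total is -0.25, the ratio is -0.5 / -0.25 = 200%. If it is +0.25, the ratio is -200%. These totals lie 0.75 / 0.72 = 1.0 and 1.25 / 0.72 = 1.7 standard errors from the truth.

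**Simulation.** M = a x T + e (SD 1) and Y = c' x T + b x M + u, with within-arm SD of Y equal to 5, 96 per arm and 10,000 trials per setting. Estimated proportion = (a x b) / total, all from the fitted values. The article gives no mediator paths, so a, b and c' are assumptions.

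| True total (points) | a, b, c' | True proportion | Outside 0-100%, all trials | Outside 0-100%, non-significant trials |
|---|---|---|---|---|
| 2 | 0.4, -2.5, -1.0 | 50% | 6% | 25% |
| 1 | 0.4, -1.25, -0.5 | 50% | 25% | 34% |
| 1 | 0.2, -2.5, -0.5 | 50% | 26% | 36% |
| 0 | 0, -2.5, 0 | undefined | 51% | 53% |
| 0 | 0.2, -2.5, +0.5 | undefined | 73% | 75% |

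A repeat run agreed to within about 3 percentage points throughout.

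In the 1-point settings about 72% of trials are non-significant. The central 95% of the estimated proportions in those trials runs over several hundred per cent in each direction: in one run, -286% to 510% in one setting and -430% to 574% in the other. These limits move between runs because the tails are heavy.

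**Other assumed paths.** On the SD scale with a = 0.3 and b = 0.4, a total effect of 0.40 gives a central 95% range of 2% to 86%, with 4% outside 0-100%. A total effect of 0.20 (1 point) gives -318% to 456%, with 29% outside.

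**The indirect effect itself.** In the 1-point setting with a 0.4 SD mediator shift it spans -1.01 to -0.11 points. With a = 0.3 and b = 0.4 its mean is 0.12 SD and its standard deviation 0.06 SD for every total effect from 0.40 down to 0. In points, that is 0.12 x 5 = 0.6 and 0.06 x 5 = 0.3.

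**Would a significance condition repair the ratio?** Among significant trials with a true 1- or 2-point effect, only 0.4-1.8% of ratios fall outside 0-100%. But significance needs an observed total of at least 1.41 points. With a true total of 1 and an indirect effect held at 0.5, the ratio could then be at most 0.5 / 1.41 = 35%. Simulated with significance and equal signs both required, about 28% of trials qualify. Their median proportion is about 28-38% against a true 50%; without the condition the medians are about 43-45%.

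**The case against.** The strongest defence is that a product of coefficients already is the indirect effect in outcome points. The bootstrapped SE can be read as belonging to that product, and the full analysis plan, which is not shown, may tabulate it. This stands in part: the sound quantity is computed under the plan, and the change concerns what is reported. But the article goes further than leaving detail open. It names the proportion as what will be determined. If the analysis plan differs, the two need reconciling.

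Three stronger readings may tempt a reader, and the article does not support them.

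- *The ratio never has a usable standard error.* At the planned 2 points only about 6% of estimates leave 0-100%. The difficulty belongs to small and null effects.
- *Mediation should not be examined without a significant total effect.* Running it regardless is defensible, since the indirect effect is estimable whatever the total. The fault lies in dividing by the total.
- *Some of the eight total effects are likely to be near zero.* The article gives no expected effects for WSAS, PHQ-9 or GAD-7, so this is possible but not shown.

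The 73% in the last table row is not an error rate either. There the direct and indirect effects cancel exactly and no true proportion exists. More generally, values beyond 0-100% can be correct when direct and indirect effects oppose each other.

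The simulation also ignores baseline adjustment. If adjustment cut the residual SD by 20% (an assumption), the 1-point share would fall from about 25% to 19-20%: smaller, but not removed.

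**Conclusion.** The concern holds for small and null total effects. The article fixes a quantity whose usefulness depends on a clearly non-zero total effect, and then requires it without that condition. About 6% of estimates fall outside 0-100% at the planned 2-point effect. At a true 1-point effect the figure is about 25% overall and about 35% in non-significant trials. At zero the proportion is undefined and its bootstrapped SE is not meaningful.

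The figures rest on 96 per arm, SD 5, no baseline adjustment and assumed mediator paths. Two different sets of paths give similar results at 1 and 2 points.

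This is a planned secondary analysis in a phase II trial. The efficacy conclusion, sample size and data collection do not depend on it.

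**What to change.** - Make the indirect effect (product of coefficients) and the direct effect, in points of each outcome with bootstrap confidence intervals, the mediation results for all four outcomes at both follow-ups, irrespective of significance.
- Keep the proportion mediated as a descriptive supplement only. Always show it with the total effect and its interval, and give it a bootstrap percentile interval in place of an SE.
- Do not interpret the proportion where the interval for the total effect includes zero or where the direct and indirect effects differ in sign.
- State that any proportion quoted only after a significant total effect tends to be too low, because that selection favours overestimated total effects.

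The cost is wording in the protocol and the analysis plan; the same models are fitted. The downside is that outcomes without a demonstrated effect get no headline percentage.

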**Methods and analysis:**

The PACT trial is a two-armed, parallel-group, multicentre RCT to assess the efficacy of PACT in comparison with usual physiotherapy care (UC). 240 patients referred to physiotherapy with CLBP will be recruited from three National Health Service (NHS) hospitals trusts. Inclusion criteria are: age ≥18 years, CLBP ≥12-week duration, scoring ≥3 points on the Roland-Morris Disability Questionnaire (RMDQ) and adequate understanding of spoken and written English to participate. Patients will be randomised to PACT or UC (120 per arm stratified by centre) by an independent randomisation service and followed up at 3 and 12 months post randomisation. The sample size of 240 will provide adequate power to detect a standardised mean difference of 0.40 in the primary outcome (RMDQ; 5% significance, 80% power) assuming attrition of 20%. Analysis will be by intention to treat conducted by the trial statistician, blind to treatment group, following a prespecified analysis plan. Estimates of treatment effect at the follow-up assessments will use an intention-to-treat framework, implemented using a linear mixed-effects model.

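### Mediation should be reported as an indirect effect in outcome points: the planned proportion mediated is unstable when the treatment effect is small, and the 3-month version cannot show direction

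*Protocol article*

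**What the plan says.** The Statistical analysis section plans a secondary analysis of mechanism. For RMDQ, WSAS, PHQ-9 and GAD-7, at 3 and at 12 months, the proportion of the treatment effect "that is mediated by the treatment effect on the process variables at 3 months will be determined". On method it says: "This will be estimated by the product of coefficients method using bootstrapped SEs". On when to run it: "This analysis will be undertaken irrespective of achieving the statistical significance". The sentence that follows turns to the case of a non-significant treatment effect, so the significance meant is that of the treatment effect.

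The Outcome measures section and Table 1 give three assessment times: baseline, 3 months and 12 months. The process variables have no post-baseline measurement before 3 months.

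**The concern.** The quantity to be reported is a ratio: indirect effect divided by total effect. The plan puts no condition on the size of the denominator. If the total effect is small, the estimated ratio can exceed 1, turn negative or change sign through sampling error alone, and then cannot be read as a proportion. A bootstrap standard error does not cure this, because a ratio whose denominator may pass through zero has no stable standard error.

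A second, narrower problem concerns the 3-month outcomes, which include the primary end point. Mediator and outcome are then answered at the same visit. A patient who is less disabled may report more acceptance because of it, and the analysis cannot tell this from acceptance reducing disability.

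At stake is the evidence on mechanism, which the article lists among its strengths and its secondary objectives. The primary efficacy test is not at stake.

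**Working it through.** **Inputs from the protocol article.** "The sample size of 240 will provide adequate power" for a standardised difference of 0.40 at 5% significance and 80% power with 20% attrition (Proposed sample size); 120 per arm (Abstract). The same section says "this equates to a 2-point difference between groups", so the implied SD is 2/0.40 = 5 RMDQ points. Two-sided testing is assumed.

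**The plan's own figure first.** Analysed per arm: 120 × 0.8 = 96. SE of the total effect in SD units: √(2/96) = 0.144, or 5 × 0.144 = 0.72 RMDQ points. Power at 0.40 SD: Φ(0.40/0.144 − 1.96) = Φ(0.81) = 79%. Total N: 4 × ((1.96 + 0.84)/0.40)² = 196, and 196/0.8 = 245. Both agree closely with the stated 80% and 240.

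**The mediation ratio.** Let a be the treatment effect on the mediator, b the mediator-outcome slope given treatment, and c the total effect. The proportion is a × b / c. The article gives no values for a or b. Assumed: b = 0.5 in SD units, and a true proportion of 0.375 in every scenario, so a = 0.375 × c / 0.5. Trials were simulated at 96 per arm with within-arm SDs of 1, one mediator, no covariates and no clustering.

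| True total effect | a | 95% sampling range of the proportion | Non-significant trials with proportion outside 0 to 1 |
|---|---|---|---|
| 0.4 SD (2 points) | 0.30 | 0.03 to 0.95 | not needed here |
| 0.2 SD (1 point) | 0.15 | -1.7 to 2.7 | about 35% |
| 0.1 SD (0.5 point) | 0.075 | -4.1 to 5.1 | about 47% |

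The outer limits in the last two rows move by a few tenths between simulation runs, which is itself a sign of the ratio's heavy tails.

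**The reason in one line.** At a true total effect of 0.2 SD, the chance that the estimated total effect has the wrong sign is Φ(−0.2/0.144) = Φ(−1.39) = 8%. At 0.1 SD it is Φ(−0.69) = 24%.

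**The indirect effect in the same setting.** At 0.2 SD, a × b has a 95% sampling range of about -0.07 to 0.22 SD, which is -0.35 to 1.1 RMDQ points at an SD of 5.

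**At a total effect of exactly zero (b = 0.5).**
- No effect on the mediator: indirect effect -0.14 to 0.14 SD; proportion -5.3 to 5.8, with 50% of estimates outside 0 to 1.
- True indirect effect of 0.20 SD cancelled by an opposite direct effect: indirect effect 0.06 to 0.36 SD, clearly above zero; proportion about -22 to 22, with 94% outside 0 to 1. The ratio hides a finding that the product shows.

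**Same visit, 3-month outcomes.** Suppose the mediator has no causal effect on the outcome, so the true proportion is 0, and the total effect is 0.4 SD.
- The outcome drives the mediator with slope 0.5 and treatment has no other effect on the mediator. Then a = 0.5 × 0.4 = 0.2, the fitted b is 0.5, and the proportion is 0.2 × 0.5 / 0.4 = 0.25.
- An unmeasured common cause gives a correlation of 0.5, and a = 0.4. Then the proportion is 0.4 × 0.5 / 0.4 = 0.5.

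Simulated medians were 0.25 and 0.49.

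**The case against.** The best defence is that the decision to run mediation whatever the significance is correct. An indirect effect is well defined without a significant total effect, and the planned product of coefficients estimates it directly. That stands. A reader might infer from the sentence on significance that the analysis should be dropped when the trial is null; the protocol does not support that reading. The fault lies only in the scale of reporting.

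Several other strong readings also fail:

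- **That all the mediation is same-visit.** The plan sets 3-month process variables against outcomes at each follow-up, so the time-ordered analysis with 12-month outcomes is already there.
- **That adjustment for baseline mediator and outcome is missing.** The article says an approved statistical analysis plan exists. It is not shown, and model covariates are a detail it may hold.
- **That bootstrapped standard errors commit the trial to symmetric intervals.** No interval type is stated, and percentile intervals come from the same resamples.
- **That the instability is far worse than shown.** Holding a at 0.3 while the total effect falls puts 48% (0.2 SD) and 71% (0.1 SD) of non-significant trials outside 0 to 1. But the true proportions are then 0.3 × 0.5 / 0.2 = 0.75 and 0.15/0.1 = 1.5, so these figures mix opposing direct effects with estimation error. The figures under working hold the true proportion fixed.
- **That the ratio is meaningless at the design effect.** At 0.4 SD, a range of 0.03 to 0.95 is very imprecise, but not meaningless.

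It is also fair to say that this is a secondary analysis, and that no earlier mediator measurement exists to repair the 3-month model.

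**Conclusion.** The point holds for the reporting scale and, for 3-month outcomes only, for direction. As written, the plan commits to a ratio that is unstable in the null or small-effect case in which it insists on reporting it: at 0.2 SD roughly a third of non-significant trials would give a proportion that is not a proportion, and at 0.1 SD nearly half. The indirect effect, from the same model, remains usable throughout.

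The sizes rest on an assumed slope of 0.5, an assumed true proportion of 0.375, 96 analysed per arm and a simple two-group comparison. A more efficient model would shrink the SE of 0.144 and move the trouble to smaller effects, but would not remove it at zero. The size of the same-visit distortion rests on the assumed slope or correlation of 0.5. The inability to establish direction follows from the visit schedule alone.

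The change should be made, but its reach is limited to the mechanism analysis. The primary RMDQ comparison and the sample size are untouched.

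**What to change.** 1. Make the indirect effect (product of coefficients, in points of each outcome scale, with a percentile bootstrap confidence interval) the reported mediation quantity, irrespective of significance.
2. Report the proportion mediated only where the confidence interval of the total effect excludes zero. Even then, present it as a rough summary beside the indirect effect: selecting on significance favours large estimated denominators. With a true total effect of 0.2 SD half mediated, the median proportion among significant trials was 0.37 against a true 0.5.
3. Describe the 3-month mediator to 3-month outcome results as associational. Rest causal statements about mechanism on the 3-month mediator to 12-month outcome analysis already planned. Time order settles which was measured first; it does not remove common causes of mediator and outcome, so those statements still need that caveat.

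The cost is wording. No new data or visits are needed, and the bootstrap resamples are those already planned. The downside is that there is no single percentage to quote when the effect is null or small, and that the main mechanism statement waits for 12-month data.

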## Ethics and dissemination

### Ethical issues

The trial will be conducted in accordance with current guidelines for ethical research conduct and subject to full Research Ethics Committee (REC) approval (National Research Ethics Committee South Central—Berkshire; 14/SC/0277), including any provisions of site-specific assessment, and local research and development approval. It will comply with the International Conference for Harmonisation of Good Clinical Practice (ICH GCP) guidelines and the Research Governance Framework for Health and Social Care. The trial is registered on a trial registry (ISRCTN95392287) and the lead site (Guy's & St Thomas' NHS Foundation Trust; GSTT) will audit this project annually to ensure compliance with the necessary legislation.

All patients in the trial will benefit from receiving physiotherapy for their CLBP. This is a very low-risk study as both treatments are non-invasive and delivered by appropriately qualified physiotherapists. Patients attending PACT sessions should visit hospital less often and will receive additional resources to aid self-management of their condition, possibly reducing its impact on participants' lives. This may lead to benefits for society and the NHS, such as reduced healthcare usage and less time off work, which is important in such a widespread and costly condition. The disadvantage of taking part is the additional time spent completing the questionnaires and for some patients an interview. These should not take more than 60 min in total to complete. Potential participants will be fully informed of the trial procedures before entering the study via a patient information sheet.

#### Informed consent

Potential participants will be identified by clinical physiotherapists from each hospital centre, informed about the RCT in writing and invited to participate. The physiotherapist will explain that participation is completely voluntary and that they are free to refuse involvement. They will be given at least 24 hours to consider whether they would like to participate. The RAs will then contact them to see if they are interested in participating and answer any questions about the study, prior to conducting the screening process and signing the consent form.

#### Fair access

Any adult patient referred to physiotherapy with low back pain lasting over 12 weeks and good English will be eligible for the trial. Participants will be able to complete measures online, by post or in person, so they should not be disadvantaged if they do not have access to the internet.

### Dissemination

The results of this study will be communicated to participants at the end of the study and disseminated via peer-reviewed publications, patient interest groups and conference presentations. The results will enable clinicians, patients and health service managers to make informed decisions regarding the efficacy of PACT for patients with CLBP. However, further studies will be necessary to demonstrate the generalisability of the findings beyond physiotherapy services in London and the South East, as well its effectiveness and cost-effectiveness.

### Service user involvement

CLBP patients have been involved in the design of the PACT trial and service users have contributed to the development of the patient guide. Participants from the feasibility study have also provided input and feedback on the proposals for this RCT. One of them is now the patient and public involvement (PPI) representative for this study, providing ongoing input (informal feedback and participating in TSC meetings) to ensure it addresses issues relevant to users.

